### Exclusion criteria

2.5

Those with peripheral neuropathy, ulcers, and gangrene of the limbs caused by various other reasons (e.g., hypothyroidism, alcohol, drugs, heredity, etc.), or those with a history of skin ulcers or lesions that do not heal easily.Women who are in preparation for pregnancy, during pregnancy, or breastfeeding.Those with acute complications such as combined diabetic ketoacidosis, lactic acidosis, severe infections, etc.Those who suffer from serious liver or kidney damage or serious cardiovascular and cerebrovascular diseases (angina pectoris, myocardial infarction, multiple cerebral infarctions, cerebral hemorrhage, etc.).Those who have scars or pigmentation on the skin of the testing site, will affect the accuracy of the test.Those who are participating in other acupuncture or drug clinical trials.

### Withdrawal criteria

2.6

If adverse drug reactions, acupuncture-related adverse events, significant physiological changes, or severe complications or deterioration of the condition arise during the research process, and a professional physician evaluates that continued participation is inadvisable, the researcher must terminate the study.The patient is noncompliant and refuses to adhere to the therapy regimen.Participant voluntarily requests to withdraw.

Researchers must diligently record the rationale and timing of individuals’ removal from the trial. Individuals who have undergone more than half of the treatment regimen (≥4 sessions) should be incorporated into the efficacy analysis.

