#### Moxibustion groups

2.9.2

Both moxibustion groups will receive the same conventional treatment (mecobalamin and epalrestat) as the control group, with moxibustion as an add-on therapy. In the 15-min moxibustion group, the selection of acupoints is based on traditional Chinese medicine literature (28), moxa cones will be pasted on the acupoints, and moxibustion will be applied by ignition, each time for 15 min at each acupoint, once every three days, twice a week, four consecutive weeks of treatment. To ensure standardization, the moxa cone will be kept at a distance from the skin that elicits a warm sensation without causing pain or burning, and this distance will be consistently maintained by the practitioner.

The 30-min moxibustion group will follow the same operation as the 15-min moxibustion group apart from the intervention duration.

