#### Primary outcome

2.10.1

Total clinical effective rate

Overall clinical effectiveness will be assessed at 2 time points: at week 4 and during the follow-up period (month 1). These specific time points are chosen to evaluate the immediate therapeutic effects following the completion of the 4-week treatment course and to determine the short-term sustainability of these effects 1 month after the intervention has ceased. It will be classified into the following 3 grades according to the Guidelines for Clinical Study of New Chinese Medicines:

Cure: clinical symptoms such as limb numbness, coldness and chilling pain, sensory abnormalities, muscle weakness, and muscle atrophy disappear, tendon reflexes return to normal, and the total score of TCSS is ≤ 5 points;Effective: numbness of the limbs, cold and chilling pain, sensory abnormalities, muscle weakness myasthenia, and other clinical symptoms significantly improved, tendon reflexes returned to normal, TCSS score level 2 or 1 level lower;Ineffective: clinical symptoms did not improve or worsen, tendon reflexes were not elicited, and TCSS score grade did not decrease or increase.

Total effective rate = [(number of cured cases + number of effective cases)/total number of cases] × 100%.

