#### Statistical analysis

2.10.3

Statistical analysis of the data will be performed by a third-party statistician who will not involved in the pre-test, using the statistical software IBM SPSS Statistics version number (SPSS 26.0). Measurement information to meet the normal distribution of the use of the mean ± standard deviation table, counting information is expressed in the number of cases (%). The non-parametric rank sum test was employed for group comparisons, while chi-square analysis will facilitate additional group comparisons. Furthermore, a mixed linear model, COX regression analysis, and logistic regression analysis will be utilized for the exploratory examination of factors influencing the primary outcome indices. For missing data handling, multiple imputation will be employed for primary outcome analyses. A *p*-value of less than 0.05 indicates that the differences are statistically significant. Statistical analyses will be conducted by qualified statisticians. Upon completion of data entry and review, statisticians must finalize the statistical analysis promptly and produce a written report detailing the findings.

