#### Sample size estimation

2.10.4

The sample size was calculated based on the primary outcome, defined as the clinical effectiveness rate. Drawing from prior studies and pilot data, the effectiveness rate for the conventional treatment group was estimated at 60%, while the moxibustion groups were hypothesized to achieve an effectiveness rate of 90%. A two-sided test was adopted with a significance level (*α*) of 0.05 and a statistical power (1-*β*) of 90%, ensuring adequate sensitivity to detect the specified effect size, the calculation yielded a minimum of approximately 24 participants per group. To accommodate an anticipated dropout rate of 20%, the sample size was adjusted upward to 30 participants per group. With three study groups, this results in a total sample size of 90 participants.

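### Patients withdrawn because their neuropathy worsened, and not assessed afterwards, are excluded or imputed and are not counted as Ineffective

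*Protocol article*

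**What the plan says.** Four statements in the protocol article bear on this point.

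- **Section 2.6, Withdrawal criteria.** A patient may be taken out when "severe complications or deterioration of the condition arise during the research process" and a physician judges that continuing is inadvisable. The reason must be kept: "Researchers must diligently record the rationale and timing of individuals’ removal from the trial".
- **Section 2.6, last sentence.** "Individuals who have undergone more than half of the treatment regimen (≥4 sessions) should be incorporated into the efficacy analysis". By implication, withdrawn patients with fewer sessions are not included.
- **Section 2.10.1, Primary outcome.** The failure grade reads "Ineffective: clinical symptoms did not improve or worsen, tendon reflexes were not elicited, and TCSS score grade did not decrease or increase". The outcome is "Total effective rate = [(number of cured cases + number of effective cases)/total number of cases] × 100" per cent, and the total is not defined further.
- **Section 2.10.3, Statistical analysis.** "For missing data handling, multiple imputation will be employed for primary outcome analyses". No exception is made by reason for withdrawal.

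Table 1 places the primary outcome at week 4 and month 1. It shows no assessment at withdrawal, and no section says whether withdrawn patients are still seen at the scheduled visits.

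**The concern.** For a patient withdrawn because the neuropathy worsened, the trial holds information that points to failure, and it records the reason. The stated rules do not use that information. With fewer than four sessions, the patient falls outside the efficacy analysis. With four or more sessions and no later assessment, the grade is missing and is imputed. Neither route counts a failure.

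This type of loss is related to the outcome, so handling it like any other gap raises the effective rate of the arm where it occurs. It could also differ between arms. Exposure is none, 15 min or 30 min. The Discussion describes moxibustion accidents as fairly common and names burns, infection and allergy in patients with reduced temperature sense. Section 2.8 leaves treating staff and patients unblinded, so a decision to stop may be made with the allocation known. Both the add-on comparison and the comparison of durations, which is the trial's central question, could be affected.

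**Working it through.** **Inputs**

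- Success rates (2.10.4): "the effectiveness rate for the conventional treatment group was estimated at 60" per cent, and 90% for the moxibustion groups.
- Patients per arm (2.10.4): 30, with 20% anticipated dropout from all causes, so 0.20 × 30 = 6 per arm.
- Sessions (2.9.2): "once every three days, twice a week, four consecutive weeks of treatment", so 2 × 4 = 8, in the moxibustion arms only.
- Number withdrawn for worsening DPN and not assessed afterwards: not given. Call it *w* per arm and take 1 to 6, where 6 means the whole anticipated dropout.

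**The plan's own figure.** The dropout step reproduces: 24 / (1 − 0.20) = 30. The 24 does not. With two-sided α 0.05 and 90% power, the pooled formula gives [1.960 × √(2 × 0.75 × 0.25) + 1.282 × √(0.24 + 0.09)]² / 0.30² = 41.7, that is 42 per group. That is a separate matter. What follows uses only the 30 per arm.

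**Step 1: the rate as the plan would report it.** Let *p* be the success rate among the 30 − *w* observed patients.

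- Exclusion: p(30 − w) / (30 − w) = p.
- Imputation at the observed rate: [p(30 − w) + p·w] / 30 = p.

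Both routes return 60% and 90%, whatever *w* is. Exclusion removes a failure from the denominator. Imputation credits on average 0.6 or 0.9 of a success per patient.

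**Step 2: the rate with these patients counted as Ineffective.** p(30 − w) / 30.

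| w | Conventional | Overstated by | Moxibustion | Overstated by |
|---|---|---|---|---|
| 1 | 58% | 2 points | 87% | 3 points |
| 3 | 54% | 6 points | 81% | 9 points |
| 6 | 48% | 12 points | 72% | 18 points |

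Per patient this is 0.60/30 = 2 points and 0.90/30 = 3 points.

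**Step 3: the difference between a moxibustion arm and conventional treatment.** With failures counted, the difference in points is 30 − 3w(moxibustion) + 2w(conventional).

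| w conventional | w moxibustion | Difference (reported: 30) |
|---|---|---|
| 3 | 3 | 27 |
| 6 | 6 | 24 |
| 0 | 3 | 21 |
| 3 | 0 | 36 |

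For 15 min against 30 min, with 90% observed in both arms and three such withdrawals in one arm only, a gap of 90 − 81 = 9 points would be reported as zero.

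**Step 4: does it matter that 60% and 90% are planned as group rates?** Suppose they already include three such failures per arm. There are then 18 successes among 27 observed patients (66.7%) and 27 among 27 (100%). The reported rates are too high by 6.7 and 10 points, or 2.2 and 3.3 per patient. The size is about the same.

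**Step 5: the session rule.** Four of eight sessions is exactly half, while the sentence in 2.6 asks for more than half. The conventional arm has no moxibustion sessions, so the rule cannot be applied alike in all arms. It also sits unreconciled beside the imputation rule in 2.10.3: a patient left out under one is a missing outcome under the other.

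**The case against.** The strongest case against runs as follows.

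**These are not known failures.** A reader might infer that the plan turns established failures into successes. The documents do not support that. Section 2.6 speaks of the condition and does not limit deterioration to the neuropathy. The Ineffective grade joins symptoms, tendon reflexes and TCSS grade, and a physician's judgement that continuing is unwise settles none of these fully. This stands: such patients are likely failures, and only those whose neuropathy worsened are at issue.

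**Withdrawn patients may still be assessed.** Nothing in the protocol ends assessment at withdrawal, and including those with at least four sessions is compatible with later assessment. This stands too. The point is confined to patients not assessed afterwards.

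**The imputation model may use the reason.** The article gives one sentence on imputation, and the model is properly left to an analysis plan that is not shown. A model using the recorded reason would shrink the bias. This stands for the imputation route. It does not help patients with fewer than four sessions, whose exclusion is implied by a rule in the article itself.

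**The size is assumed.** The share of dropout due to worsening is not given. A case with all six losses in one moxibustion arm and none in the control arm would give 60% against 72%, or 12 points. That treats the whole all-cause dropout as one type in one arm. It is an extreme and no expectation.

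**Harm is not failure.** A patient stopped for an adverse event is not thereby Ineffective, and harms are reported separately in 2.10.5. This is right, and such patients should not be graded as failures automatically.

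**Conclusion.** The point holds in limited form. Followed as written, the rules exclude or impute a patient withdrawn for worsening neuropathy who is not assessed afterwards, although worsening belongs to the failure grade and the reason is on record. The arm's effective rate is then overstated by about 2 points (conventional) or 3 points (moxibustion) per such patient out of 30. This assumes 60% and 90% among observed patients, an imputation model that ignores the reason, and that each such patient would in fact have been graded Ineffective.

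It would go too far to conclude that the plan favours moxibustion. The arm-level error is upward, but the error in the difference depends on where the withdrawals fall. With three in the conventional arm only, the plan would understate the benefit, at 30 points against 36.

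**What to change.** Amend sections 2.6, 2.10.1 and 2.10.3 before outcome data are analysed by group:

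1. Analyse the primary outcome in all randomised patients, and say that this is the total in the effective-rate formula.
2. Count withdrawal for worsening of DPN as Ineffective at that and later time points, using the recorded reason.
3. Keep the scheduled week-4 and month-1 assessments for other withdrawn patients where they agree.
4. Use multiple imputation for all remaining missing primary outcomes, including adverse-event withdrawals without an assessment, so that no group is left without a rule.
5. Reconcile the four-session rule in 2.6 with the imputation rule in 2.10.3.

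These changes concern how outcomes are counted. They do not touch when a patient should be stopped.

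**Cost.** Mostly wording, since the reason is already collected. It must be recorded specifically enough to separate worsening of DPN from other deterioration. Seeing withdrawn patients at the scheduled visits takes some effort but adds no visit to Table 1. Effective rates will be somewhat less favourable, by the 2 or 3 points per patient shown above.

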### Study design

2.1

This trial is a multi-clinical center, open method, randomized controlled trial (RCT), three-arm, parallel-group design. The study is designed to assess moxibustion as an add-on therapy to conventional treatment. This study protocol obtained approval from the Ethics Committee of the Third Hospital Affiliated with Zhejiang University of Traditional Chinese Medicine and has been registered with the Clinicaltrials registry (identification code: NCT06330233). This trial protocol is developed in accordance with the Standard Protocol Items: Recommendations for Interventional Trials (SPIRIT) guideline. The schedule of this trial is presented in Table 1, and the flow diagram of the study is shown in Figure 1.

**Table 1 tab1:** Schedule of enrolment, interventions and outcome assessments.

Study period	Baseline	Treatment phase (4 weeks)		Follow-up phase (1 month)
The time point	Week 0	Week 2	Week 4	month 1
Eligibility screening	√			
Demographic information	√			
Case data	√			
Inclusion criteria	√			
Exclusion criteria	√			
Moxibustion treatment		√	√	
Outcomes assessment				
(1) Total clinical effectiveness			√	√
(2) Electrophysiological examination	√		√	
(3) TCSS	√		√	√
(4) VAS	√		√	√
(5) TCMS	√		√	√
(6) Infrared thermography testing	√		√	
Safety evaluation		√	√	

√, required; TCSS, Toronto Clinical Scoring System; VAS, visual analog scale; TCMS, traditional Chinese medicine syndrome score scale.

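### Section 2.6 makes refusal of the regimen, and physician-judged harm or worsening, grounds for removal and provides for no outcome assessment afterwards, so some retained moxibustion patients may need an imputed primary outcome

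*Protocol article*

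**What the plan says.** All references are to the protocol article.

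- **Section 2.6, Withdrawal criteria.** Three grounds stand side by side: adverse reactions, complications or deterioration where "a professional physician evaluates that continued participation is inadvisable, the researcher must terminate the study"; non-compliance with refusal of the regimen; and the participant's own request. For all of them, "Researchers must diligently record the rationale and timing of individuals’ removal from the trial". The section then adds: "Individuals who have undergone more than half of the treatment regimen (≥4 sessions) should be incorporated into the efficacy analysis".
- **Section 2.9.2, Moxibustion groups.** Sessions are given "once every three days, twice a week, four consecutive weeks of treatment".
- **Section 2.1, Table 1, and section 2.10.1.** The primary outcome, "Total clinical effectiveness", is ticked at week 4 and at month 1. At week 2 the table shows treatment and safety evaluation but no efficacy outcome.
- **Section 2.10.3, Statistical analysis.** "For missing data handling, multiple imputation will be employed for primary outcome analyses". The imputation model is not described.
- **Section 2.10.4, Sample size estimation.** "To accommodate an anticipated dropout rate of 20%, the sample size was adjusted upward to 30 participants per group". The assumed effective rates are 60% with conventional treatment and 90% with moxibustion.
- **Section 2.9.4, Concomitant care.** A participant who receives further treatment for DPN is excluded.
- **Section 2.10.5, Safety assessment.** Clinicians decide on discontinuing the trial after an adverse reaction. The course of the event is recorded; efficacy assessment is not mentioned.

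**The concern.** The first two grounds in section 2.6 are reasons to stop treatment. Refusal of the regimen is listed apart from a request to withdraw, so the protocol itself recognises patients who stop treatment without asking to leave. It still removes them, and it does not say that their outcome is collected. Section 2.6 also keeps those with enough sessions in the efficacy analysis. The plan therefore retains patients without providing for their primary outcome to be observed.

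Stopping for harm, worsening or refusal is plausibly related to outcome. It may also be related to arm. The Discussion describes moxibustion accidents as fairly common and links burns and infection to reduced temperature sensation in diabetic patients, so 30 minutes could stop more patients than 15. The documents give no rates by arm. If stoppers do worse than patients who stayed and are imputed as though they were alike, the arm with more stoppers looks better than it is. This bears mainly on 15 versus 30 minutes, the comparison the trial is meant to settle. An analysis plan can choose an imputation model, but it cannot recover outcomes that were never collected.

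Patients who ask to withdraw altogether are outside this point. In the tablets-only arm there are no sessions to count; there the point is only that stopping tablets and stopping assessment are not distinguished.

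**Working it through.** **1. Who is affected.** Sessions: 2 per week × 4 weeks = 8 (section 2.9.2). A partial course that meets the stated minimum of 4 means stopping after session 4, 5, 6 or 7. Four of eight is exactly half, whereas section 2.6 also speaks of more than half, so the lower bound may be 5. This does not change the point.

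**2. What is observed for them.** The first efficacy outcome after baseline is at week 4. Session 4 falls at about the end of week 2. The week-4 visit is then at most about 4 − 2 = 2 weeks away, and the month-1 visit about 2 + 4 = 6 weeks away. Both are calendar visits that such a patient can still attend. Without them, only baseline data exist.

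**3. How many (assumption-based).** The plan's dropout step reproduces: 24/(1 − 0.20) = 30, so the allowance is 0.20 × 30 = 6 per arm. The plan gives no reasons or timing for dropout. Assume that all 6 stop treatment, spread evenly over the 8 possible stopping points (0 to 7 completed sessions):

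- lower bound of 4 sessions: 6 × 4/8 = 3 per moxibustion arm;
- lower bound of 5 sessions: 6 × 3/8 = 2.25.

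The number is 0 if all dropouts stop early or ask to withdraw. Three is a working upper figure under an even spread, not a strict limit.

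**4. 15 versus 30 minutes (illustration).** Assume 90% effective among patients who stayed in both arms, stoppers only in the 30-min arm, imputation at 90%, and 30 analysed per arm.

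- Shift per stopper if truly ineffective: (0.90 − 0)/30 = 3.0 points.
- Shift per stopper if 60% of stoppers are effective: (0.90 − 0.60)/30 = 1.0 point.

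| Ineffective stoppers | True 30-min rate | Rate after imputation |
|---|---|---|
| 1 | 29 × 0.9/30 = 87% | 90% |
| 2 | 28 × 0.9/30 = 84% | 90% |
| 3 | 27 × 0.9/30 = 81% | 90% |

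Standard error of the difference at 90% each: √(2 × 0.9 × 0.1/30) = 7.7 points. Per stopper this is 3.0/7.7 = 0.39 or 1.0/7.7 = 0.13 standard errors. The extreme corner, three ineffective stoppers all in one arm, gives 9 points, or 9/7.7 = about 1.2 standard errors. Equal numbers of similar stoppers in the two moxibustion arms cancel.

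**5. Moxibustion versus conventional treatment (illustration).** Assume equal numbers of ineffective stoppers in both arms, with control stoppers also retained and imputed at 60%. The control shift is (0.60 − 0)/30 = 2.0 points each, giving true rates of 58%, 56% and 54%. The true differences for 1, 2 and 3 per arm are 87 − 58 = 29, 84 − 56 = 28 and 81 − 54 = 27 points, against 30 after imputation. The overstatement is 1 point per pair.

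**The case against.** A reader might infer that the protocol bars assessment after removal, so that these outcomes are certain to be lost. The text does not go that far. It requires reason and timing to be recorded and does not say that nothing else may be. The sentence keeping patients with at least 4 sessions in the analysis can even be read as presupposing that their outcome is taken. Section 2.10.6 refers to an implementation plan and operating procedures that are not shown, and early-termination visits may be described there. The harm clause is also tied to continued participation being inadvisable; it does not say that pausing moxibustion alone removes a patient. Removal for stopping treatment is clearest for refusal of the regimen. All of this stands, and it is why the point is conditional on removal being applied as written.

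A second tempting reading is that the trial's main comparisons would be materially biased. That is not supported either. The imputation model is unseen, and one that used adherence or the reason for stopping could behave differently. The number affected may be zero, and moxibustion versus conventional treatment barely moves.

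A third objection is that section 2.9.4 would exclude a patient who starts other DPN treatment after stopping, so that collecting outcomes alone would achieve little. This is right, and the fix has to address it.

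The objections do not remove the stated rule. Removal is explicit, retention in the analysis is explicit, and no outcome is scheduled in between. Whether an outcome is collected is decided while the trial runs and cannot be left to the analysis.

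**Conclusion.** The point holds in a limited form, as a worthwhile and cheap improvement. Loss of the outcome is inferred from the removal rule and the visit schedule; it is not stated. The effect is probably small, and the per-stopper figures rest on assumed numbers, an assumed even spread of stopping, and assumed imputation at the rate of patients who stayed. It grows if several poor-outcome stoppers fall in one arm. The direction could favour the arm with more stoppers if they do worse than those who stayed; it would reverse if they do better.

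**What to change.** - **Sections 2.6 and 2.10.5.** Separate *stops study treatment* from *withdraws consent to assessment*. State that a patient in any arm who stops moxibustion or tablets is still assessed by the blinded assessor at the existing week-4 and month-1 visits, unless consent to assessment is withdrawn. State that observed values are used instead of imputed ones.
- **Section 2.9.4.** State that a patient who starts other DPN treatment after stopping is also still assessed, with that treatment recorded, and is not dropped from follow-up.

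The physician's judgement on when to stop treatment and the ≥4-session rule are left unchanged.

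**Cost.** Wording in the protocol and operating procedures, with no new visit, procedure or participant. Sites must recall patients who have stopped treatment. While the ≥4-session rule stands, the gain in the moxibustion arms is limited to patients who stop after about sessions 4 to 7 and return.

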### Blinding

2.8

This study will not employ blinding for administrators and patients across different moxibustion groups due to the particular characteristics of moxibustion manipulation. However, this study will be blind to the group assignment of outcome assessors made by a specifically designated person.

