#### Conventional treatment group

2.9.1

Mecobalamin tablets (0.5 mg/dose, 3 times/day) and epalrestat (0.5 g/dose, 3 times/day) will be administered orally for 4 weeks in conjunction with the patient’s daily treatment (basal medication treatment for patients with combined hypertension and hyperlipidemia).

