#### Concomitant care and intervention

2.9.4

During the study period, participants must avoid other DPN interventions, including behavioral therapies and medications, that could influence the study’s outcomes. Participants will be excluded if they receive additional combined interventions for the treatment of DPN. Participants with comorbid conditions, including hypertension, diabetes, and other chronic diseases, may maintain their standard medications and therapies. Research personnel will document the names of comorbid conditions, medications, and therapies in the case report form.

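### Entry to the efficacy analysis depends on receiving at least 4 moxibustion sessions, a post-randomisation condition with no stated equivalent in the tablet-only arm

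*Protocol article*

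**What the plan says.** Four parts of the protocol article bear on who is analysed.

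- **Withdrawal criteria (2.6).** The reasons for withdrawal include adverse reactions or events, deterioration, the participant's own request, and non-compliance ("The patient is noncompliant and refuses to adhere to the therapy regimen"). The section then says: "Individuals who have undergone more than half of the treatment regimen (≥4 sessions) should be incorporated into the efficacy analysis".
- **Interventions (2.9.1, 2.9.2).** Moxibustion is given "once every three days, twice a week, four consecutive weeks of treatment". The conventional drugs, which all three arms take, "will be administered orally for 4 weeks"; the conventional arm has nothing that is counted in sessions.
- **Concomitant care (2.9.4).** "Participants will be excluded if they receive additional combined interventions for the treatment of DPN". The text does not say whether this means from treatment, from the trial or from the analysis.
- **Statistical analysis (2.10.3).** "For missing data handling, multiple imputation will be employed for primary outcome analyses". No population is named for this.

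The primary outcome (2.10.1) divides by the total number of cases, without saying whether these are the cases randomised or the cases analysed. Nowhere does the article say that all randomised participants are analysed in the arm assigned.

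**The concern.** Randomisation makes the arms comparable at entry. A condition that can be judged only after treatment has begun, and only in some arms, can undo this.

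The session count is such a condition. A moxibustion patient who stops after two or three sessions because of a burn, an adverse event or worsening falls below the threshold. A control patient who does equally badly has no session count to fall below. If those who stop early respond less often than those who continue, leaving them out raises the moxibustion response rate with no true effect behind it.

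The article itself gives grounds to think that stopping may relate to outcome. Deterioration and adverse events are listed withdrawal reasons in 2.6, and the Discussion says that burns, infection and allergy can arise with moxibustion in diabetic patients with reduced temperature sensation.

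If the exclusion in 2.9.4 also means exclusion from the analysis, it is a second selection after randomisation. What is at stake is the hypothesis in the Introduction, that add-on moxibustion is better than conventional treatment alone.

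**Working it through.** **1. The threshold.** 2 sessions per week × 4 weeks = 8 sessions. Half of 8 is 4. More than half would mean at least 5. A patient with exactly 4 sessions is therefore included by the figure in brackets and not included by the words before it.

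**2. Which arms it can be applied to.**

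| Arm | Sessions planned | Can the count be applied? |
|---|---|---|
| Conventional | none (daily tablets) | no; unclassifiable or kept by default |
| 15-min moxibustion | 8 | yes |
| 30-min moxibustion | 8 | yes, same wording |

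**3. Possible size under no true effect.** Inputs from Sample size estimation (2.10.4): control response 60%, 30 per group, two-sided α = 0.05, dropout 20%. The documents do not give dropout by arm or the response rate among those who stop, so both are assumed here.

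Let a share d of one moxibustion arm be removed, with response rate r among those removed, and let the true rate be 60% in both arms. Then

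rate among those kept = (0.60 − d·r) / (1 − d).

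For d = 0.20 and r = 0 this is 0.60/0.80 = 75%, an apparent benefit of 15 points. Exact enumeration of the Pearson test, with 30 controls against 30(1 − d) moxibustion patients (rounded to a whole number), gives:

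| d | r | Rate kept | Apparent benefit | Type I error |
|---|---|---|---|---|
| 0 | – | 60.0% | 0 | 4.9% |
| 5% | 0 | 63.2% | +3.2 points | 5.9% |
| 10% | 0 | 66.7% | +6.7 points | 8.3% |
| 20% | 0 | 75.0% | +15.0 points | 22.4% |
| 20% | 30% | 67.5% | +7.5 points | 9.3% |
| 20% | 60% | 60.0% | 0 | 5.3% |

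The last row is removal unrelated to outcome.

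**4. Simulation with a random number removed.** 400,000 trials per scenario, 30 per arm, 60% in both arms, each non-responder removed with the stated probability:

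| Removed, moxibustion | Removed, control | Type I error |
|---|---|---|
| 25% | 0 | 8.4% |
| 50% | 0 | 21.5% |
| 25% | 25% | about 5% |
| 50% | 50% | about 5% |
| 50% | 25% | about 10% |

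Removing 50% of non-responders loses 0.50 × 0.40 = 20% of the arm; removing 25% loses 10%. With one-sided removal at 50%, 21.4 of the 21.5 percentage points of false positives favour moxibustion.

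**5. The rule in 2.9.4, if it means exclusion from the analysis.** Take the planned rates, 60% versus 90%. Removing 25% or 50% of control non-responders lifts the control rate to 0.60/0.90 = 67% or 0.60/0.80 = 75%. Simulated power falls from about 80% to 60% or 32%. If 25% of non-responders are removed from both arms, power is about 70%.

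**The case against.** The strongest reply is that the article states less than a reader might infer. Several parts of it stand.

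- **No efficacy set is formally defined.** The sentence in 2.6 is an inclusion rule placed after the withdrawal criteria. That patients below 4 sessions are left out is implied, not written. This is right, but a minimum for inclusion has little purpose unless those below it are left out.
- **The main clause could cover a tablet course.** A share of the regimen can be read for four weeks of tablets. But the only number given is in sessions, and no measure of tablet intake is stated.
- **Only the session rule differs between arms by its wording.** The non-compliance and other-treatment rules read the same for all arms. A reader might infer that unrelieved controls will be excluded more often under 2.9.4. That is plausible, since patients are not blinded (2.8), but nothing in the article shows it. It is also open whether the exclusion is from the analysis at all.
- **The 15 versus 30 min contrast.** The session rule is worded identically for both durations, so the concern is chiefly about moxibustion versus control. The numbers removed could still differ between the two durations.
- **Imputation.** A reader might infer that 2.6 contradicts the planned multiple imputation. Section 2.10.3 names no population, so the imputation could cover everyone randomised. The sections need reconciling; a conflict is not demonstrated.
- **An analysis plan may define the sets.** It may, and silence on that would be no finding. The point rests on a rule that this document does state.
- **The larger figures are extremes.** A type I error of 21% needs all the loss to be non-responders and confined to one arm, although the 20% dropout allowance applies to every group. Equal removal in both arms brings it back to about 5%.

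**Conclusion.** The concern holds in a limited form. Section 2.6 ties entry to the efficacy analysis to a quantity that is measured after randomisation and counted only in the moxibustion arms, and its threshold is inconsistent with an 8-session course. If the rule is followed as written, the moxibustion versus control comparison may not be between randomised groups, and any resulting bias would favour moxibustion if early stoppers respond less often.

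The size cannot be fixed from the documents. With 60% response in both arms and 30 per arm, two-sided type I error runs from about 5% (removal unrelated to outcome, or equal in both arms), through about 8% (a quarter of non-responders removed from one moxibustion arm only), to about 21% (half removed from that arm only). The last is a bound under unfavourable assumptions, not a forecast.

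The documents do not support saying that the 2.9.4 rule does bias the control rate, or that both rules select on outcome as a matter of fact. What stands on 2.9.4 is that its meaning for the analysis is undefined. The point still needs correcting before analysis, because outcomes not collected from those who stop may not be recoverable later.

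**What to change.** Replace the sentence in 2.6 with:

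> The primary efficacy analysis includes all randomised participants in the arm assigned, whatever the number of sessions, compliance or other DPN treatment; week-4 and month-1 outcomes are still collected after treatment stops where the participant agrees; outcomes that remain missing are multiply imputed.

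Then:

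- Keep the session rule only for a per-protocol sensitivity analysis, with one consistent threshold and a matching tablet-intake criterion in the conventional arm.
- In 2.9.4 leave the concomitant-treatment rule itself unchanged, and add that participants to whom it applies stay in the primary analysis.
- Reconcile 2.6, 2.9.4 and 2.10.3, so that the imputation statement names the same population. State in 2.10.1 that the denominator is all randomised participants.

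The cost is wording, some follow-up of participants who stop treatment, and possibly a smaller estimated effect. The number randomised does not change.
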